**Fig. 1 Fig1:**
[figure not shown]
Study flowchart. Before arriving at ED, the eligibility of OHCA patients will be evaluated by the OHCA response team of the receiving hospital, based on on-scene information provided by EMS. For eligible OHCA patients, randomization will be completed within 5 min of arrival at ED. After CT imaging, patients of first enrollment will be checked again if any exclusion criteria are met. Only patients who received early coronary angiography and/or intervention will be included in the final analysis. ACLS: advanced cardiovascular life support; CCL: cardiac catheterization laboratory; CPC: cerebral performance category; CPR: cardiopulmonary resuscitation; CT: computed tomography; ECLS: extracorporeal life support; ED: emergency department; EKG: electrocardiography; EMS: emergency medical services; mRS: modified Rankin scale; OHCA: out-of-hospital cardiac arrest; ROSC: return of spontaneous circulation; ECG: echocardiography

Randomization is performed immediately upon ED arrival (target: within 5 min) for patients meeting inclusion criteria and experiencing refractory cardiac arrest (defined as ongoing CPR on arrival). Patients with stable ROSC before randomization (defined as sustained pulse with systolic BP ≥ 90 mmHg without ongoing chest compressions for ≥ 2 min) are not randomized and proceed directly to coronary angiography.

Patients with unstable ROSC defined as: (1) return of pulse but requiring ongoing chest compressions, (2) recurrent VF/VT requiring repeated defibrillation, (3) persistent profound hypotension with systolic BP < 90 mmHg or mean BP < 60 mmHg despite vasopressor support, or (4) intermittent epinephrine injection to maintain the heart beating are eligible for randomization."

A computerized randomization list is provided by the National Taiwan University Hospital Clinical Trial Center by a software app (REDCAP). The randomization is in 1:1 ratio, stratified by participant hospitals, with a permuted block of 4. In-hospital randomization is conducted by OHCA response team coordinators immediately after the eligible patients arrive at ED. The randomization codes will be maintained by the National Taiwan University Hospital Clinical Trial Center and monitored by the Data Safety Monitoring Committee. The EMS teams and intensivists in the cardiac intensive care unit (ICU) will be blinded to the study group assignment and follow the institutional standards for post-cardiac arrest care.

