#### Post resuscitation protocol

After initial stabilization at ED, electrocardiography and echocardiography would be arranged to identify cardiac causes for OHCA. Computed tomography would be arranged (either before or after cath intervention) to exclude non cardiac causes of OHCA or contraindication (Table 1). All patients without contraindications for coronary intervention will then be transferred to the cardiac catheterization laboratory (CCL) for coronary angiography. With successful emergent management, patients are admitted to the cardiac ICU for continued post-cardiac arrest care.

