#### Study endpoints

The primary endpoint is defined as 30-day survival with Cerebral Performance Category (CPC) score of 1 or 2). The CPC score will be assessed by the designated neurologists at each participant hospital, who are blinded to the intervention received. Secondary endpoints include favorable neurological status (modified Rankin scale (mRS) < 3, crude survival and neurologically favorable survival at discharge, 3 months, and 6 months; duration of mechanical ventilation; duration of stay in ICU; duration of hospitalization; causes of hospital mortality and late mortality; and health care costs. The incidence of serious adverse events related to CPR, ECMO, coronary angiography, and LV unloading will be documented as safety endpoints.

For patients still hospitalized at 30 days, bedside assessment is performed. For discharged patients, assessment is conducted during scheduled follow-up clinic visits or via structured telephone interview using validated instruments.

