### Statistical analysis

#### Sample size rationale

The trial is designed to demonstrate a treatment effect on the primary endpoint. Accepting a power of 80% and a level of significance of 5%, the sample size is calculated using a two-sided chi-square test. In reference to published multicenter trials, we estimate a 30-day neurologically favorable survival of 25% and 12% in the emergency total ECLS group and the standard ACLS with rescue ECMO group, respectively. Assuming a 10% dropout rate, we plan to enroll 186 participants per arm (roughly 200). No interim analysis is planned. If interim analysis is deemed necessary determined by Consortium committee, we will conduct one interim analysis 1 year after enrollment, and the statistical testing will be adjusted to this accordingly. The flowchart of intention to treatment and per protocol are attached in supplement.

All patients enrolled in the study will be analyzed primarily on an intention-to-treat basis. Continuous variables will be reported as mean ± standard deviation or median with interquartile range. Categorical variables will be presented as frequency. A logistic regression model with the stratification variable (center) will be conducted to evaluate the primary efficacy endpoint by treatment group. Odds ratios are to be calculated as effect estimates with 95% confidence intervals. Patients whose primary outcome cannot be assessed will be regarded as failures.

Per-protocol analysis, which only includes patients who adhere to the allocated protocol, will be performed to minimize the impact of non-adherence or deviations from the strict protocol.

For patients randomized to the total ECLS group, if ECPR is not required due to stable ROSC at ED or ECMO is initiated after 20 min since arriving at ED or after 60 min since emergency calls, they would be excluded from per-protocol analysis. Similarly, for patients randomized to the standard ACLS with rescue ECMO group, if ECMO is initiated within 20 min of arriving at the ED or within 60 min of emergency calls, they would be considered crossover and excluded from per-protocol analysis.

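### The Fig. 1 caption limits the final analysis to angiography recipients, which contradicts the stated intention-to-treat analysis and could bias the result in either direction if applied

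*Protocol article*

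**What the plan says.** Two places in the protocol article define who is analysed.

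- **Fig. 1 caption:** "Only patients who received early coronary angiography and/or intervention will be included in the final analysis". The sentence before it adds a second eligibility check: "After CT imaging, patients of first enrollment will be checked again if any exclusion criteria are met".
- **Statistical analysis (under Sample size rationale):** "All patients enrolled in the study will be analyzed primarily on an intention-to-treat basis", and "Patients whose primary outcome cannot be assessed will be regarded as failures".

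The order of events is also given. "Randomization is performed immediately upon ED arrival (target: within 5 min"). The allocated strategies follow (Intervention—ECMO initiation): VA-ECMO within 15 min of randomisation in one arm; in the other, 15 min of ACLS, then a fresh look at futility, then rescue ECMO. Angiography comes after stabilisation in the ED (Post resuscitation protocol): "All patients without contraindications for coronary intervention will then be transferred to the cardiac catheterization laboratory (CCL) for coronary angiography".

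Table 1 has a separate column of exclusion criteria that apply after randomisation.

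**The concern.** A randomised patient who dies in the ED, or is judged futile before reaching the catheterisation laboratory, is a failure under the statistics section and is absent under the caption. One primary result cannot follow both rules.

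The caption's rule selects on something that happens after randomisation. ROSC, ECMO and the futility decision all come before angiography, and the arms differ by design in how they pass through those steps. A comparison among angiography recipients therefore loses the protection of randomisation.

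The trial is open-label. Two published analysis sets also leave room to choose between them once results are known.

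**Working it through.** **1. Could both statements describe the same patients?**

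| Randomised patient | Statistics section | Fig. 1 caption |
|---|---|---|
| Dies in the ED before angiography | In, as a failure | Out |
| Judged futile before angiography | In, as a failure | Out |
| Has angiography, dies by day 30 | In, as a failure | In, as a failure |
| Has angiography, CPC 1 or 2 at day 30 | In, as a success | In, as a success |

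They differ in the first two rows. The caption is not the per-protocol set either: the statistics section defines that set by ECMO timing, crossover and stable ROSC without ECPR, and never by angiography.

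**2. Inputs**

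- Endpoint: 30-day survival with CPC 1 or 2 (Study endpoints).
- Planned rates 25% (ECLS) and 12% (control), two-sided 5% chi-square test, 186 per arm (Sample size rationale).
- Assumed, because the article gives no figure: the share *c* of each arm that reaches angiography.
- Assumed: nobody who misses angiography has a favourable outcome.
- Assumed for the no-effect case: 18.5% in both arms, the mean of the planned rates, (25 + 12)/2.

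**3. Baseline, all randomised patients analysed**

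Odds ratio = (0.25/0.75)/(0.12/0.88) = 2.44.

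Power uses the pooled two-proportion test. SE under the null = 0.0403, so the critical difference is 1.96 × 0.0403 = 0.0789. SE under the alternative = 0.0397. Power = Φ((0.130 − 0.0789)/0.0397) = 0.90. This is above the stated 80%, since 186 exceeds what 25% v 12% needs at 80% power with 10% dropout (139/0.9 = 155). That is a separate matter and does not affect this point.

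**4. Angiography-only analysis**

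Analysed rate = *p*/*c*; analysed number = 186 × *c*.

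Worked case, 85% ECLS and 60% control:
- Rates: 0.25/0.85 = 29.4% and 0.12/0.60 = 20.0%.
- Numbers: 186 × 0.85 = 158 and 186 × 0.60 = 112.
- Odds ratio: (0.294/0.706)/(0.200/0.800) = 1.67.
- Power: critical difference 1.96 × 0.0539 = 0.1056; Φ((0.0941 − 0.1056)/0.0524) = 0.41.
- No true effect: 0.185/0.85 = 21.8% and 0.185/0.60 = 30.8%. The test rejects 39% of the time, nearly always in favour of control.

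| Reaching angiography, ECLS/control | Analysed rates | OR | Power | False-positive rate, no true effect |
|---|---|---|---|---|
| All randomised | 25.0% v 12.0% | 2.44 | 90% | 5% |
| 90%/90% | 27.8% v 13.3% | 2.50 | 91% | 5% |
| 90%/80% | 27.8% v 15.0% | 2.18 | 79% | 9% |
| 90%/70% | 27.8% v 17.1% | 1.86 | 58% | 22% |
| 85%/60% | 29.4% v 20.0% | 1.67 | 41% | 39% |
| 70%/90% | 35.7% v 13.3% | 3.61 | 99.5% | 22% |

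In the last row the false positives favour ECLS. With equal shares the odds ratio hardly moves, though the risk difference rises from 13.0 to 14.4 percentage points.

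**The case against.** The statistics section names the primary analysis clearly: intention to treat, logistic regression with centre, unassessable outcomes as failures. The caption says final, not primary. The figure itself is not visible, and the intention-to-treat and per-protocol flowcharts are said to be in a supplement that is not shown. If the statistics section governs, the primary result is unaffected and the fault is one stray sentence. That stands as a limit on the consequence. It does not remove the contradiction: the caption states a rule, and that rule matches neither analysis set in the text.

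One could also read enrolled patients as those confirmed after the CT check. The intention-to-treat set would then itself be selected after randomisation, and a patient who meets no exclusion but dies before angiography would still be handled in two ways.

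A reader might infer that the caption would bias the result against early ECLS, because ECMO brings to angiography patients who would otherwise die in the ED. The article does not support that as a fact. The comparator includes rescue ECLS, so the planned contrast is mainly one of timing, and no share reaching angiography is given for either arm. Fewer control patients may well reach it, given the 15 min of ACLS and the second futility check, but the size of any gap is unknown and the reverse is possible.

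The larger figures in the table need gaps of 20 to 25 points. The no-effect case also requires unequal access to angiography to yield no extra favourable survivors. Both are possible; neither is documented.

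**Conclusion.** The contradiction is certain, and the caption's rule is wrong for a primary analysis. Whether it would do harm depends on which text governs. If the caption were applied, the result could be biased in either direction: the odds ratio runs from 1.67 to 3.61 against 2.44, power from 41% to 99.5%, and the false-positive rate from 5% to 39% over the shares examined. These figures rest on assumed shares reaching angiography, on no favourable outcome without angiography, and on 186 analysed per arm before any dropout (about 167 per arm would give 87% power at baseline). A 10-point gap (90%/80%) already lifts the false-positive rate to about 9%. Neither a definite direction nor a single headline loss of power can be claimed from the article. The point should be corrected before analysis, because it decides who counts in the primary endpoint.

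**What to change.** 1. Delete the caption sentence.
2. State in the statistics section that the primary analysis includes every randomised patient in the assigned arm, whether or not angiography was done.
3. Reconcile this with the post-randomisation exclusion column of Table 1 and with the recheck after CT, so that those exclusions do not remove patients from the primary set. Deleting the caption sentence alone would leave these two in conflict with an all-randomised set.
4. If an angiography-only analysis is kept, label it descriptive.

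The cost is wording in the caption, Table 1 and the statistics section, with matching text in the analysis plan and supplement. It needs no new patients and no change to clinical care; patients excluded after randomisation must still have their 30-day outcome recorded, and the article already plans follow-up of all enrolled patients.

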#### Intervention—ECMO initiation

After randomization, if the enrolled patient has stable ROSC before initiating ECMO, he/she will be transferred to the cardiac catheterization laboratory (CCL) without ECMO support. The indications for ECMO include no ROSC or unstable ROSC (persistent or recurrent VF or pVT, profound cardiogenic shock with systolic blood pressure (BP) < 90 mmHg or mean BP < 60 mmHg despite intense inotropic support (bolus of epinephrine > 3 bolus), or persistent hypoxia with arterial oxygen saturation (SaO2) < 90% despite maximal ventilation support). The femoral artery and vein access will be cannulated under ultrasound guidance. ECMO would be deemed futile if more than one discontinuation criterion suggesting ineffective resuscitation (end-tidal carbon dioxide < 10 mmHg, partial pressure of oxygen in arterial blood < 50 mmHg or oxygen saturation < 85%, or serum lactate > 20 mmol/L) has been met.

However, if unstable ROSC persists as defined above, ECMO is initiated according to the randomization arm protocol. For the emergency total ECLS group (Fig. 1), the veno-arterial ECMO (VA-ECMO) will be initiated within 15 min after randomization. For standard ACLS with the recue ECMO group, patients will receive 15 min of ACLS at ED first. If there is no stable ROSC, the futility of ECLS would be reevaluated. Therefore, the recue VA-ECMO should be initiated after 15 min since randomization.

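### The stable-ROSC and unstable-ROSC definitions overlap with no stated precedence, and the ECMO section words the boundary differently again

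*Protocol article*

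**What the plan says.** In the protocol article, Enrollment and randomization of trial population (text after the Fig. 1 legend), stable ROSC before randomisation is "defined as sustained pulse with systolic BP ≥ 90 mmHg without ongoing chest compressions for ≥ 2 min". Such patients "are not randomized and proceed directly to coronary angiography".

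The next paragraph lists four forms of unstable ROSC, joined by *or*:
- "1) return of pulse but requiring ongoing chest compressions"
- "2) recurrent VF/VT requiring repeated defibrillation"
- "persistent profound hypotension with systolic BP < 90 mmHg or mean BP < 60 mmHg despite vasopressor support"
- a last item that closes the sentence with its consequence: "intermittent epinephrine injection to maintain the heart beating are eligible for randomization"

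The label is used twice more. Under Intervention—ECMO initiation, "if the enrolled patient has stable ROSC before initiating ECMO, he/she will be transferred to the cardiac catheterization laboratory (CCL) without ECMO support". The same paragraph gives its own account of unstable ROSC as an indication for ECMO. Under Statistical analysis (Sample size rationale), a patient in the total ECLS group leaves the per-protocol set "if ECPR is not required due to stable ROSC at ED".

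**The concern.** The two definitions carry opposite consequences, so they should not both apply to one patient. Stable ROSC is defined by pulse, systolic pressure and time without compressions. Unstable ROSC adds mean pressure, drug support and rhythm. The stable definition does not require these features to be absent, and no sentence ranks one definition above the other.

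The same boundary does three jobs: it decides who is randomised, whether ECMO is started after allocation, and who stays in the per-protocol set. The first decision is made by site coordinators at eight hospitals, with a target of five minutes from arrival. The second is made with the arm known, because the trial is open-label. The third acts on the total ECLS arm only. If the text can be read two ways, sites can enrol different patients, and ECMO delivery and per-protocol membership can depend on the reading chosen.

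**Working it through.** The plan gives no figure on this point to reproduce, so the check applies the definitions to cases.

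**1. Overlap through mean pressure.** Inputs from the enrolment section: stable needs systolic ≥ 90 mmHg; the third unstable item is met by mean < 60 mmHg despite a vasopressor. The article does not say how mean pressure is obtained. I assume the usual approximation, mean = (systolic + 2 × diastolic)/3.

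Mean < 60 then requires diastolic < (180 − systolic)/2:

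| Systolic (mmHg) | Both rules met when diastolic is below (mmHg) |
|---|---|
| 90 | 45 |
| 100 | 40 |
| 110 | 35 |
| 120 | 30 |

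Example: 100/35 gives (100 + 70)/3 = 56.7 mmHg. With a pulse, at least two minutes without compressions, and this pressure persisting on a vasopressor, the patient is both excluded and eligible.

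**2. How much depends on the word *sustained*.** Hold the three stable conditions as met. Four yes/no features remain: mean < 60, vasopressor, recurrent VF/VT, intermittent epinephrine. That gives 2 × 2 × 2 × 2 = 16 combinations. The unstable definition fails only when there is no recurrent VF/VT, no intermittent epinephrine, and not both a low mean and a vasopressor, which is 3 combinations. So 16 − 3 = 13 meet both definitions. Of these, 4 × 3 = 12 include recurrent VF/VT or intermittent epinephrine. If a pulse in those circumstances is read as not sustained, those 12 drop out and 13 − 12 = 1 remains, the mean-pressure case in step 1. The overlap shrinks on that reading but does not vanish. These are counts of logical combinations, not patient frequencies.

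**3. Enrolment section against the ECMO section.**

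| Feature of unstable ROSC | Enrolment section | ECMO initiation section |
|---|---|---|
| Low pressure | Systolic < 90 or mean < 60 on a vasopressor | Same pressures, but on intense inotropic support, glossed as more than three epinephrine boluses |
| Epinephrine | Intermittent injection, no number, an item of its own | Only as the bolus count attached to low pressure |
| Oxygenation | Not used | SaO2 < 90% on maximal ventilation |

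The ECMO section does not redefine stable ROSC, so the enrolment definition is the only one available there. Two hypothetical patients show the effect:
- 110/70 mmHg, three minutes without compressions, SaO2 86% on maximal ventilation. Mean = (110 + 140)/3 = 83.3 mmHg. This patient is stable by the enrolment definition, so goes to the catheterisation laboratory without ECMO, yet has an ECMO indication by saturation.
- 100/35 mmHg on a vasopressor after two epinephrine boluses. This patient is unstable by the enrolment section. If the bolus count is read as a condition, the patient does not meet the low-pressure item in the ECMO section.

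**4. Per-protocol set.** A stable-ROSC exclusion is stated for the total ECLS group. For the standard ACLS group the stated exclusion concerns early ECMO only. A borderline patient called stable therefore leaves the set in one arm and, on the stated rules, stays in it in the other.

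**The case against.** The case on the other side has five parts.

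- **A pulse held by drugs is not sustained.** A pulse kept going by repeated epinephrine, or interrupted by recurrent VF/VT, is naturally read as failing the stable definition. This is a fair reading and it removes those overlaps. It leaves the mean-pressure case and the saturation case.
- **The ECMO section points towards unstable.** It lists mean pressure < 60 mmHg among its indications and says that persisting unstable ROSC leads to ECMO according to the arm. That is some guidance after allocation. It is not a stated precedence, and the criteria differ from those used at enrolment.
- **There is no real gap.** A reader might infer that a patient with systolic pressure below 90 mmHg, no vasopressor and no compressions falls under no rule. The documents do not support this. The general entry rule is CPR still under way on arrival, and only stable ROSC is taken out of it. Such a patient is randomisable if CPR was under way on arrival and fails the entry rule if it was not.
- **The primary comparison is protected.** A reader might infer that open-label staff bias enrolment between arms. Allocation is not known at the eligibility decision, so open-label status alone does not do that, although fixed blocks of four within hospital make some allocations deducible. Randomisation is stratified by hospital, the primary model includes centre, and the primary analysis is by intention to treat. Differences between sites in whom they enrol therefore alter case mix and not the comparison between arms. This stands.
- **The article condenses a fuller protocol, and its flowchart is not shown.** True, but both definitions are printed with numerical limits and opposite consequences. The point is a conflict in stated text, not missing detail.

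**Conclusion.** The point holds as an inconsistency in the stated definitions. At least one type of patient (systolic ≥ 90 mmHg, mean < 60 mmHg despite a vasopressor) is both excluded and eligible. After allocation the differing ECMO wording creates further patients who are stable and unstable at once. Intermittent epinephrine may add to the overlap, depending on how *sustained* is read.

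What is exposed is the definition of the enrolled population, the delivery of ECMO once the arm is known, and per-protocol membership, where the label is applied to one arm only. The intention-to-treat comparison is not undermined.

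The size cannot be given. Any percentage would need a distribution of early post-ROSC pressures, the share of patients on vasopressors and the share with persisting hypotension, and the documents contain none of these. The conclusion rests on the wording, on the usual formula for mean pressure, and on carrying the enrolment definition of stable ROSC into the ECMO and per-protocol rules, since no other is given. It should be corrected, because it concerns an entry criterion and the correction is small.

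**What to change.** Reconcile the enrolment and ECMO initiation sections into one classification in which every patient with ROSC falls into exactly one class, and state which criterion prevails when several apply. One way is to define one class as ROSC that does not meet the criteria of the other. Refer to that single classification, without rewording it, in the enrolment rule, the ECMO initiation rule, the per-protocol rule and the randomisation form. In the per-protocol paragraph, also say how standard ACLS patients with the same label are handled. The pressure, drug-support and oxygenation limits are for the clinical team to set; this review proposes none.

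The cost is a one-paragraph protocol clarification and a matching field in the randomisation form, with no extra patients or data.

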**Design, setting, and participants:**

This is a prospective, investigator-initiated, multicenter, open-label randomized clinical trial conducted in eight experienced extracorporeal membrane oxygenation (ECMO) centers in the Taipei metropolitan area. Eligible adults aged 18–75 years with witnessed refractory shockable OHCA (ventricular fibrillation or pulseless ventricular tachycardia) who received bystander cardiopulmonary resuscitation (CPR) are randomized 1:1 on emergency department (ED) arrival.

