## Study design

This is an investigator-initiated, multicenter, open-label, interventional randomized clinical trial. The responsible investigator is the **Taipei Metro Out-of-Hospital Cardiac Arrest Total Care**
*Consortium.*

The trial has been registered on ClinicalTrials.gov (NCT06692075).

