### Enrollment and randomization of trial population

Refractory OHCA is defined as cardiac arrest in patients transported to hospital with ongoing CPR. Upon receiving the EMS’s referral of OHCA patients, the OHCA response team, composed of emergency physicians, interventional cardiologists, and cardiac surgeons, will evaluate the eligibility of patients based on on-scene information. The inclusion and exclusion criteria are described in Table 1. When the patient arrives at the ED, a rapid screening is performed to reassure his/her eligibility. All eligible patients will be randomized into the emergency total extracorporeal life support (total ECLS) group and the standard advanced cardiac life support with rescue ECMO (**standard ACLS**) group (Fig. 1).

**Table 1 Tab1:** PreInclusion and exclusion criteria

Screening inclusion criteria	Pre randomization Exclusion	Post-randomization exclusions criteria
• Aged 18–75 years old	• Age under 18 or over 75	• Age < 18 years or > 75 years old
• Witnessed cardiac arrest with bystander cardiopulmonary resuscitation	• Major trauma	• Initial non-shockable rhythm, i.e. pulseless electrical activity or asystole
• Initial shockable rhythm, i.e. ventricular fibrillation or pulseless ventricular tachycardia	• Initial non-shockable rhythm	• Acute aortic dissection
• Need for repeated defibrillation shocks (> 2) by external defibrillator	• Major trauma	• Acute massive pulmonary embolism
• Estimated transportation time from activation of the emergency response system to arrival at emergency department of participant institutions less than 60 min	• Suicide, illicit drug overdose or intoxication	• Acute intracerebral hemorrhage
	• Pre-arrest mRS > 3 or CPC > 2	• Major trauma due to blunt, penetrating or burn injury
	• Unwitnessed CPR	• Severe peripheral artery disease
		• Known pregnancy
		• Suicide, illicit drug overdose or intoxication
		• Known pre-arrest mRS > 3 or CPC > 2
		• Active malignancy with a life expectancy of less than 1 year
		• Effective DNR order
		• Absolute contraindications to emergency coronary angiography, including known anaphylactic reaction to angiographic contrast media, acute bleeding

CPC, cerebral performance category; DNR, do-not-resuscitation; mRS, modified Rankin score

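### A single published block size of 4 within each hospital makes a third of allocations deducible in an open-label trial, exposing enrolment to selection bias

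*Protocol article*

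**What the plan says.** The allocation method is given in the protocol article, in the text after Fig. 1 under Enrollment and randomization of trial population: "The randomization is in 1:1 ratio, stratified by participant hospitals, with a permuted block of 4". One block size is named. Nothing says that it varies or is kept from the sites, and the article itself makes it public.

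The same section says who allocates: "In-hospital randomization is conducted by OHCA response team coordinators immediately after the eligible patients arrive at ED". The OHCA response team, made up of emergency physicians, interventional cardiologists and cardiac surgeons, also "will evaluate the eligibility of patients based on on-scene information", and a rapid screen follows on arrival.

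On blinding, Study design says: "This is an investigator-initiated, multicenter, open-label, interventional randomized clinical trial". The section on randomization adds that "The EMS teams and intensivists in the cardiac intensive care unit (ICU) will be blinded to the study group assignment", and Study endpoints adds the neurologists who score CPC. The enrolling team is not listed. Custody of the list is central: "The randomization codes will be maintained by the National Taiwan University Hospital Clinical Trial Center and monitored by the Data Safety Monitoring Committee".

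The trial is "conducted in eight experienced extracorporeal membrane oxygenation (ECMO) centers in the Taipei metropolitan area", so there are eight strata.

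**The concern.** A permuted block of 4 in a 1:1 trial must contain two patients per arm. Once both places of one arm are used, the rest of the block is known. A central list hides the sequence itself, but it does not stop deduction from allocations already seen. Here each part of that deduction is available at the hospital: the block size is published, stratification by hospital means that local history is enough, and the two arms are visibly different to the team that delivers them.

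There is also room to act on a prediction. Stable ROSC before randomization keeps a patient out of the trial, while unstable ROSC lets the patient in. Pre-arrest function, intoxication and estimated transport time have to be judged quickly from incomplete information. A team that expects a particular arm could, even without intent, lean one way on a borderline patient.

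If that happens, the arms differ in prognosis before treatment starts. The planned intention-to-treat analysis and the centre-adjusted logistic regression act only on randomized patients, so neither can recover those withheld beforehand.

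**Working it through.** The article gives no figure for predictability, so there is none to reproduce.

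**Inputs from the article**
- 1:1 allocation, fixed block of 4, stratified by hospital (Enrollment and randomization of trial population).
- Eight hospitals (Abstract).
- 186 patients per arm, rounded in the text to about 200; assumed favourable outcome 25% versus 12% (Sample size rationale). These serve only to give scale.

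**Share of allocations known with certainty.** A 2:2 block has 6 equally likely sequences.
- AABB and BBAA: positions 3 and 4 are both determined, so 2 certain allocations each.
- The other four sequences: only position 4 is determined, so 1 certain allocation each.
- Mean per block = (2×2 + 4×1)/6 = 1.333. Share = 1.333/4 = **33.3%**.

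**Share guessed correctly** by someone who always names the arm with more places left and tosses a coin when they are equal:
- Position 1: 0.5.
- Position 2: 2/3, because two of the three remaining places belong to the other arm.
- Position 3: (1/3)×1 + (2/3)×0.5 = 2/3.
- Position 4: 1.
- Sum = 0.5 + 0.667 + 0.667 + 1 = 2.833. Share = 2.833/4 = **70.8%**, against 50% by chance.

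**Scale**
- 2 × 186 = 372 patients; 372/3 = 124 allocations deducible in advance (400/3 = about 133 if 200 per arm are enrolled).
- With equal recruitment over eight hospitals, which is an assumption, each randomizes 372/8 = 46.5 to 400/8 = 50 patients, of which about 15 to 17 are deducible.
- Under the planning rates the expected favourable outcomes are 186×0.25 = 46.5 and 186×0.12 = 22.3. The designed difference is about 24 patients, so steering a modest number of good-prognosis patients would matter.

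Patients excluded after randomization still use up a place in the list, so those exclusions do not disturb the count.

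**Alternatives.** The fixed block of 6 was enumerated exactly. The mixed sizes were simulated (48 patients per hospital, 3,000 replicates, sizes drawn with equal probability) against an observer who knows the possible sizes, records every allocation and updates the probabilities after each one.

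| Scheme | Known with certainty | Guessed correctly |
|---|---|---|
| Fixed 4 (article) | 33.3% | 70.8% |
| Fixed 6 | 25.0% | 68.3% |
| Random 4, 6 | about 5.6% | about 69.0% |
| Random 4, 6, 8 | about 2.2% | about 67.7% |

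A larger fixed block helps little with certainty. Varying the size removes almost all of it.

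**The case against.** The strongest counter-argument is practical. The article does not say that whoever is on duty knows the ordered history of the hospital's allocations. Sites work round the clock, teams are multidisciplinary, and each enrols only about 46 to 50 patients on equal recruitment. The list is central, randomization is targeted within 5 minutes of arrival, and all eligible patients are to be randomized. Many criteria are factual or measurable: age, rhythm, witnessed arrest, number of shocks, and a defined blood pressure and duration for stable ROSC. Some of the discretionary criteria appear again as exclusions after randomization, when the arm is already known and block size makes no difference. Lastly, varying the block size lowers the correct-guess rate only from about 71% to about 68%.

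Most of this stands as a limit on likelihood. The 33.3% and 70.8% are ceilings for a complete tracker, and the gain in guess rate is small. It does not remove the exposure. The coordinators who randomize are the people best placed to keep count. Eligibility is assessed before arrival as well as in the 5-minute window. ROSC stability, pre-arrest function and intoxication still leave judgement before randomization. Certain predictions are also the easiest to exploit, and these are what varying sizes nearly remove.

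**Conclusion.** The point holds. A fixed, disclosed block of 4 within hospital, in an open-label trial where the unblinded site team both judges eligibility and randomizes, makes on average 33.3% of allocations deducible with certainty and 70.8% guessable. Both figures are exact for a block of 4 and assume an observer who has followed every allocation at the hospital; they fall if tracking is incomplete. The per-hospital counts also assume equal recruitment.

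The documents establish a risk of selection bias. They do not show that it has happened and give no basis for estimating its effect on the primary endpoint. This is a weakness that should be corrected because it is cheap to do so; it does not by itself invalidate the trial.

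**What to change.** For all remaining allocations, the Clinical Trial Center should generate a new list with block sizes varying at random within hospital (for example 4, 6 and 8), keep the stratification by hospital, and withhold the sizes from sites and public documents until database lock. The protocol should then say only that blocks vary in size and that the sizes are not disclosed.

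This needs a new list in the existing randomization software and a protocol amendment. It adds no patients, no visits and no change in care. The maximum within-hospital imbalance rises from 2 patients (half a block of 4) to 4 (half a block of 8), which is minor at 46 to 50 patients per hospital. The article does not report how far recruitment has gone, so the benefit depends on how many allocations remain.
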